### 3.3. Stepped wedge diagram

Table 2 shows the achieved stepped wedge sample for all 10,666 patients who were enrolled in the trial, including CS and OBGyn patients, regardless of whether they were followed up. Note cohort 1, which has only one hospital as described above. The implementations were completed in orderly fashion over the planned 18 months, and the split of observations between control and implementation periods were as expected, for an overall split of 54% in control and 46% in the implementation period.

Table 2: Achieved stepped wedge sample, total and by cohort

| Hospitals        | Implement-
ation date | N      | 2021           |   |   |   |   | 2022          |          |   |            |   | 2023                |   |            |   |          |   |   |   |  |  |  |  |
|------------------|--------------------------|--------|----------------|---|---|---|---|---------------|----------|---|------------|---|---------------------|---|------------|---|----------|---|---|---|--|--|--|--|
|                  |                          |        | A              | S | O | N | D | J             | F        | M | A          | M | J                   | J | A          | S | O        | N | D | J |  |  |  |  |
| 1 Hospital 1     | 28-Dec-21                | 1,002  | 230, 23%       |   |   |   |   |               | 772, 77% |   |            |   |                     |   |            |   |          |   |   |   |  |  |  |  |
| 2 Hospital 2 & 3 | 1-Mar-22                 | 2,652  | 948, 36%       |   |   |   |   |               |          |   | 1,704, 64% |   |                     |   |            |   |          |   |   |   |  |  |  |  |
| 3 Hospital 4 & 5 | 9-May-22                 | 1,934  | 959, 50%       |   |   |   |   |               |          |   |            |   | 975, 50%            |   |            |   |          |   |   |   |  |  |  |  |
| 4 Hospital 6 & 7 | 11-Jul-22                | 3,089  | 2,002, 65%     |   |   |   |   |               |          |   |            |   |                     |   | 1,087, 35% |   |          |   |   |   |  |  |  |  |
| 5 Hospital 8 & 9 | 13-Sep-22                | 1,989  | 1,576, 79%     |   |   |   |   |               |          |   |            |   |                     |   |            |   | 413, 21% |   |   |   |  |  |  |  |

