|                  |                          |       | Control period |   |   |   |   | Run-in period |          |          |      |            | Intervention period |          |   |          |   |   |      |   |  |

However, the overall N's for auditors in table 3 are smaller than those for data collectors. Table 4 shows the follow up rate for each group, by control or intervention condition. While the auditors yielded plausible SSI estimates, their follow-up rates were only 52% overall, which we attribute to the late date that they began and the challenging context that Ethiopia represents.

Table 4: 30-day follow-up rates by control and intervention condition, data collectors vs. auditors

| Cohort | Control condition      |                       |                |                       |                | Intervention condition |                       |                |                       |                |
|--------|------------------------|-----------------------|----------------|-----------------------|----------------|------------------------|-----------------------|----------------|-----------------------|----------------|
|        | N enrolled in facility | Data collectors       |                | Auditors              |                | N enrolled in facility | Data collectors       |                | Auditors              |                |
|        |                        | N with follow-up data | Follow-up rate | N with follow-up data | Follow-up rate |                        | N with follow-up data | Follow-up rate | N with follow-up data | Follow-up rate |
| 1      | 230                    | 223                   | 97%            | 111                   | 48%            | 772                    | 761                   | 99%            | 545                   | 71%            |
| 2      | 948                    | 904                   | 95%            | 422                   | 45%            | 1,704                  | 1,611                 | 95%            | 851                   | 50%            |
| 3      | 959                    | 911                   | 95%            | 600                   | 63%            | 975                    | 912                   | 94%            | 603                   | 62%            |

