### *CS population with follow-up*

All CS patients enrolled in the study who have complete 30-day follow-up data collected by the auditors.

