## 7. General statistical considerations

### 7.1. Modeling

As stated in our protocol, we will use the statistical approach recommended by Hemming and colleagues. To estimate how the intervention is correlated with outcomes, we will fit a mixed effects logistic regression model of the form:

$$Outcome_{ij} = \beta_0 + \beta_1 Month + \beta_2 Intervention + \beta_x X + \mu_i + \varepsilon_{ij}$$

Where:

|                       |                                                                                                                                                     |
|-----------------------|-----------------------------------------------------------------------------------------------------------------------------------------------------|
| Outcome ij | Binary variable for the j th patient in the i th cohort, where 1 = had the adverse outcome, and 0 = did not have the outcome. |
| Month                 | Fixed categorical variable with 18 levels, one for each month. Reference category will be either the first or last month of the study.              |
| Intervention          | Fixed binary variable, where 1 = procedure occurred under intervention condition, 0 = procedure occurred under control condition.                   |
| X                     | Vector of fixed demographic and clinical controls                                                                                                   |
| β 0-x      | Set of regression coefficients                                                                                                                      |
| μ i        | Random effect for cohort                                                                                                                            |
| ε ij       | Error term for the j th patient in the i th cohort                                                                            |

Since this is a cross sectional design (no repeated measures on patients over time), we will not need to account for patient-level correlation over time. The random effect for cohort will account for the within-cluster variance, assuming one shared ICC. We will consider adding a random cohort-by-month interaction term, which would allow for different within-period and between-period ICCs.

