## 7.2. Controls

The protocol lists potential control variables for the analysis, but we will not be able to include them all in the model. We collected these variables because they may be clinically relevant, but they are difficult to collect in Ethiopia because medical records are poor and not every patient receives extensive prenatal care. In many cases, these clinical variables are collinear with emergency operations. Table 6 lists all the controls along with their final inclusion in the model or reason for exclusion from the model.

The final list of eight fixed controls will be: age, hypertension, gestational diabetes, rupture timing, emergency vs. elective, wound classification, ASA classification, and indication.

Table 6: Control variables

| Control variables listed in the protocol | Actual inclusion in our statistical model                               |
|------------------------------------------|-------------------------------------------------------------------------|
| Demographic                       |                                                                         |
| Age                                      | Include as categorical variable                                         |
| Gestational age                          | Drop due to poor data quality                                           |
| Gravida/parity                           | Drop due to poor data quality                                           |
| Pregnancy comorbidities                  |                                                                         |
| Hypertension                             | Include as binary                                                       |
| Pre-eclampsia                            | Drop here because it appears as one option under indication for surgery |
| Gestational diabetes                     | Include as binary                                                       |
| Obesity                                  | Drop due to low rate of obesity diagnosis in study population           |
| Malnourishment                           | Drop due to low rate of malnourishment diagnosis in study population    |
| Other comorbidities                      |                                                                         |
| HIV                                      | Drop due to low rate of HIV diagnosis in study population               |

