### 8.3 Aim 2: Improved compliance with infection prevention practices

Using the total intraoperative population, we will report percentages of compliance for each of the six key areas of infection prevention in the control and intervention groups. Then, we will construct six models using each binary in turn as the dependent variable, and dropping the vector of demographic variables, which are not likely to be causally related to compliance. If the estimated OR of a behavior being performed under the intervention is greater than 1 and statistically significant, then we will conclude a positive effect of the intervention on that behavior. Finally, we will fit a last model using “high compliance” (defined as a compliance score of >4) as the outcome.

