### 8.4 Aim 3: Reduced maternal postoperative mortality

We will build this model using the CS population with follow-up, and the outcome will be maternal mortality within 30 days of procedure. We expect maternal deaths to be rare and note that the study is not powered to detect a change in such a rare event. Otherwise, the model features and interpretation will be the same as the primary model.

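### The maternal mortality model (Aim 3) keeps the full primary model and its significance rule for an outcome likely to supply fewer than one death per coefficient, with no sparse-data provision

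*Combined protocol and SAP*

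**What the plan says.** SAP 8.4 (Aim 3) takes 30-day maternal death as the outcome in the CS population with follow-up. It says deaths are expected to be rare and that the study lacks power for them, and adds: "Otherwise, the model features and interpretation will be the same as the primary model".

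The features carried over are:
- Month, in SAP 7.1: "Fixed categorical variable with 18 levels, one for each month".
- The binary intervention term, and in SAP 7.1 a "Random effect for cohort".
- The covariates in SAP 7.2 (Controls): "The final list of eight fixed controls will be" age, hypertension, gestational diabetes, membrane rupture, urgency, wound class, ASA class and indication.

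The interpretation carried over is the SAP 8.2 rule that an OR below 1 with statistical significance is a positive effect. Each p-value is judged at 0.05 without adjustment (SAP, Multiple comparisons).

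The population in SAP 6 is "All CS patients enrolled in the study who have complete 30-day follow-up data collected by the auditors". SAP 4.3 says of the auditors that "their follow-up rates were only 52% overall".

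The SAP does change the model elsewhere. SAP 8.3 fits the compliance models after "dropping the vector of demographic variables", and Table 6 drops several covariates because few patients had the condition. Neither step is taken for maternal death because of its rarity. The sensitivity analyses in SAP 9 concern surgical infection.

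**The concern.** A logistic model with more coefficients than events is prone to separation. A month or covariate level with no deaths has no finite coefficient. If no deaths fall in one phase among the months that contain both phases, the intervention OR is zero or infinite. The SAP does not say what the analyst should then do. Low power is a different matter: an underpowered model still gives an estimate and an interval, whereas a separated one may give neither, or give output that depends on the software.

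At stake is a secondary endpoint that Table 5 assigns to this analysis. Without a stated fallback, the model reported for maternal death would be chosen after the deaths are known, and a formal decision rule would be applied to it. Aim 1 is not affected.

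**Working it through.** **Denominator.** Table 4 gives 2,764 control and 2,828 intervention patients with auditor follow-up: 5,592 of 10,666, or 52.4%, which reproduces the SAP's 52%. (Table 3 prints a total of 5,525, or 51.8%, although its cells also sum to 5,592. The two should be reconciled; the 1.2% difference does not matter here.) The 5,592 is a ceiling for Aim 3. Table 4's enrolled counts sum to the number that SAP 3.3 describes as "all 10,666 patients who were enrolled in the trial, including CS and OBGyn patients", and the CS-only number is not given.

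**Coefficients.** 17 month + 1 intervention + at least 8 controls = at least 26 besides the intercept. Age, wound class, ASA class and indication are categorical, so the real number is probably higher.

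**Deaths (assumed).** The protocol's Background and Rationale gives 401 maternal deaths per 100,000 live births. This is a national ratio, not a risk after CS. The 0.1% and 0.2% risks are assumptions.
- 5,592 × 0.1% = 5.6
- 5,592 × 0.2% = 11.2
- 5,592 × 0.401% = 22.4

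The results below use D = 6, 12 and 22 deaths.

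**Empty months.** With deaths spread evenly, the expected number of months with none is 18 × (17/18)^D.

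**Intervention OR.** With month as a factor and no cohort effect, only months containing both phases inform the OR. I spread Table 4's counts evenly over each cohort's months, with control ending December 2021, February, May, July and September 2022 and intervention starting February, April, June, August and October 2022. Eight months (February to September 2022) then contain both phases, with about 1,176 control and 1,378 intervention patients, or 21.0% and 24.6% of 5,592. With Poisson deaths and no effect, before controls:

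P(OR zero, infinite or undefined) = exp(−0.210D) + exp(−0.246D) − exp(−0.457D)

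| | D = 6 | D = 12 | D = 22 |
|---|---|---|---|
| Deaths per coefficient (D/26) | 0.23 | 0.46 | 0.85 |
| Months with no death, of 18 | 12.8 | 9.1 | 5.1 |
| Deaths in two-phase months (0.457D) | 2.7 | 5.5 | 10.0 |
| P(OR zero, infinite or undefined), formula | 45% | 13% | 1.4% |
| Same, simulated | 45% | 12% | 1.4% |
| Simulated upper/lower 95% limit ratio when finite | 145 | 53 | 19 |

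A separation check with eight one-coefficient controls (assumed prevalences, fixed death counts, 150 runs each) gave 35%, 9% and 1%. A fixed count gives lower figures than Poisson deaths; without controls, the same layout with exactly 6 deaths gives 40%. Three other run-in layouts, without controls, gave 49–62% at 0.1%, 16–25% at 0.2% and 1–4% at 0.4%. Across all variants the ranges are about 35–62%, 9–25% and 1–4%.

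**The case against.** The strongest reply is that the SAP already says the outcome is rare and underpowered, so a poor estimate is no surprise. That is true of imprecision: at 22 deaths the OR is nearly always finite and the problem is mainly a wide interval. It does not cover separation, and it does not withdraw the significance rule.

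A reader might infer that most month terms cannot be estimated and that the OR is unusable. The documents do not support this across the range. At 6 deaths about 13 of 18 months are empty, but at 22 only about 5 are. An empty month also loses only its own coefficient and does not by itself make the intervention OR inestimable.

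The death count is open to challenge as well. Other readings of the same protocol section move it widely. Taking 15% of the national ratio gives 5,592 × 0.401% × 0.15 = 3.4 deaths. Dividing that by the quoted CS rates of 21.4%, 10.6% and 1.9% gives about 16, 32 and 177. At 32, deaths per coefficient rise to 1.2 and about 3 months are empty. At 177 (3.2% of patients) the problem would largely go, but that is hard to square with an outcome the SAP calls rare.

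The significance rule was not shown to cause false claims. In the check without controls and with no true effect, Wald p-values fell below 0.05 in 0.05% to 3% of runs, under the nominal 5%. The case against the rule is that it can hardly return an informative answer either way.

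**Conclusion.** The point holds in a limited form. SAP 8.4 applies at least 26 fixed coefficients and the Aim 1 decision rule to a rare outcome, and the SAP has no sparse-data provision for it. If the risk is 0.1% to 0.4%, deaths per coefficient stay below one. The chance of no finite OR runs from roughly a third to 60% of datasets at the low end to a few percent or less at the high end. Even when the OR is finite, its limits differ by a factor of about 19 to 145 before controls.

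This rests on assumed death risks, an audited denominator that may include non-CS cases, even spreading of patients over months, and no cohort effect. Fewer CS patients would make the data sparser. It does not show that the model fails in every scenario. This is a matter for correction in a secondary analysis and does not threaten the trial's main conclusion.

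**What to change.** For Aim 3:
- Report maternal deaths and proportions by phase, with exact confidence intervals, as the main result.
- Limit any model to the intervention, a coarse time term (step or linear) and cohort, fitted by Firth-penalised logistic regression.
- Do not apply the Aim 1 significance rule, and label the result descriptive.

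The cost is a change of SAP wording and less adjustment for time and case mix. The by-phase proportions in particular are not adjusted for calendar time, which the report should say.

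An optional, separate point is to state how deaths recorded in theatre or on the ward are counted for patients without auditor follow-up. Changing the Aim 3 population or the source of deaths would depart from the decision in SAP 4.3 to use the auditors' data for follow-up measures, and the change proposed here does not need it.

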### 8.5 Aim 4: Reduced neonatal mortality

We will build this model using the CS population with follow-up, and the outcome will be neonatal mortality within 30 days of procedure. While our study protocol states we would capture this data prior to the mother’s discharge, we observed a significant proportion of neonatal deaths after the mother was discharged from the hospital, likely reflecting a longer

clinical course for an unwell neonate than a healthy mother. We agreed to include neonatal mortality collected up through 30 day phone follow-up. We expect neonatal deaths to be rare and note that the study may not have the power to detect a change. Otherwise, the model features and interpretation will be the same as the primary model.

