**Secondary:**

2. *Surgical infections following obstetric and gynecologic operations*: Number of patients undergoing obstetric and gynecologic operations diagnosed with postoperative infection in hospital or up to 30 days post surgery; measured by change pre and post intervention
3. *Compliance with infection prevention practices*: Number of patients undergoing obstetric and gynecologic surgery receiving each of the six perioperative infection prevention and control practices defined by the Clean Cut program; measured by change pre and post intervention
4. *Reoperation following obstetric and gynecologic surgery*: Number of patients requiring reoperation or return to the operating theatre prior to discharge following obstetric and gynecologic surgery; measured by change pre- and post-intervention

5. *Length of Stay*: Mean and median length of stay, in days, following obstetric and gynecologic surgery; measured by change pre- and post-intervention
6. *Postoperative maternal mortality*: Number of mothers who die in hospital or up to 30 days following CS; measured by change pre- and post-intervention
7. *Postoperative mortality*: Number of women who die in hospital or up to 30 days following obstetric and gynecologic surgery; measured by change pre- and post-intervention
8. *Neonatal mortality*: Number of newborn/fetal deaths prior to discharge of mother following cesarean delivery; measured by change pre- and post-intervention

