**Outcome variables:**

- Compliance to each of the six standards of surgical site infection prevention and control:
  - skin, hand, and vaginal preparation
  - gown, glove, and drape sterility
  - antibiotic selection and timing of administration (time of dosing)
  - swab counts pre and postoperatively
  - confirmation of instrument sterility
  - use of a surgical checklist for communication
- Surgical Site Infection within 30 days
- Unplanned Reoperation
- Length of Hospital Stay
- Maternal Death within 30 days
- Postoperative Death within 30 days
- Neonatal Status at Discharge (alive or dead)

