| Primary   | 1. Infection reduction in CS                                           | Surgical infection       | In hospital: Medical records, direct observation
At 30 days: Phone call | QI
Research                                                   |
| Secondary | 2. Improved compliance with infection prevention practices             | Compliance               | Direct observation during surgery                                          | QI                                                               |
|           | 3. Infection reduction in Ob/Gyn cases                                 | Surgical infection       | In hospital: Medical records, direct observation
At 30 days: Phone call | QI
Research                                                   |
|           | 4. Reduction in unplanned reoperation                                  | Reoperation              | Direct observation, medical records, theatre logs                          | QI                                                               |
|           | 5. Reduced length of stay                                              | Length of stay           | Direct observation, medical records                                        | QI                                                               |
|           | 6. Reduced maternal postoperative mortality                            | Maternal mortality       | In hospital: Medical records, direct observation
At 30 days: Phone call | QI
Research                                                   |
|           | 7. Reduced postoperative mortality                                     | Postoperative mortality  | In hospital: Medical records, direct observation
At 30 days: Phone call | QI
Research                                                   |
|           | 8. Reduced neonatal mortality                                          | Neonatal mortality       | In hospital: mortality at time of discharge                                | QI                                                               |
| Ancillary | 9. Assessment of readiness for QI generally and CLEAN-CS in particular | Facility readiness score | Interviews, surveys                                                        | Research                                                         |

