### 3.2. As executed

Our protocol made allowance for difficulties that may arise in the field:

“Given the current pandemic as well as potential civil unrest in Ethiopia, there is the potential for unanticipated challenges to implementing the protocol as described. While every attempt will be made to maintain participation of all sites, the loss of one or more sites is a distinct possibility. Recruitment of patients may also be affected by patient volumes, supply shortages, or facility closures. Given this, we will allow each site to collect up to 92 patients per month if they are able in case of the loss of a facility in a cluster. In the case where one facility in a cluster is no longer participating in the study, we will allow the other facility to increase data collection up to 150 cases per month, if feasible and the volume allows, and adjust our comparative calculations accordingly.” (p.11)

Data collection for the trial occurred from August 2021 to January 2023. Although we were able to successfully launch the intervention in all five cohorts and observe operations for over ten thousand patients, we did encounter two main fieldwork challenges that may affect the analysis plan:

1. One hospital did not participate

One hospital was unable to carry out the data collection required to participate in the study. After several attempts to begin data collection, the hospital and study team agreed to proceed without that hospital. As specified in the protocol, we did not replace that hospital, but the other hospital in its cohort was high-recruiting and was able to meet the expected patient enrollment for the cluster.

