## 5. Study aims and endpoints

As shown in table 1, the study was planned with 1 primary endpoint, 7 secondary endpoints, and 1 ancillary endpoint. In addition, the protocol states that:

"We will undertake a planned subanalysis of patients observed early during baseline (first 2 months) and compare them to patients undergoing surgery during the final stage of the study (last 2 months) after implementation of the program has had time to take effect to assess primary and secondary outcomes." (p.9)

Table 5 lists the original aims along with two aims we added after the publication of the protocol. The first is a composite outcome of complications after caesarean section, in which we include surgical infection, maternal mortality, and neonatal mortality (Aim 5). The second is Aim 6, an analysis aimed at showing the relationship between perioperative infection prevention practices and our primary outcome, infection after caesarean section.

Finally, we plan to pursue the subanalysis stated in our protocol in a future publication. This subanalysis focuses on changes in compliance with infection prevention practices across the study in relation to secular, temporal trends. We will demonstrate the relationship between compliance and secular and temporal trends by creating a graph on compliance with infection prevention practices at four points in time: the first two months of data collection vs the final two months of the intervention and the two months prior to the start of the intervention vs the two months immediately following the intervention.

In Table 5 we also list whether each endpoint will be addressed in this analysis or in future publications. For ease of reference, we renumber the aims that are addressed in this SAP and will refer to them by this renumbering hereafter.

Table 5: Plan for addressing aims in this or future analyses

| Aim     | Endpoint | Plan | Numbering in this SAP |
|---------|----------|------|-----------------------|
| Primary |          |      |                       |

|                                                                     |                                                |                           |       |
|---------------------------------------------------------------------|------------------------------------------------|---------------------------|-------|

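### SAP 8.5 moved the neonatal endpoint to 30 days after trial deaths had been seen; Tables 5 and 7 do not flag this, and no planned model covers the protocol's before-discharge endpoint

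*Combined protocol and SAP*

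**What the plan says.** **Protocol.** Secondary outcome 8 is "Number of newborn/fetal deaths prior to discharge of mother following cesarean delivery". The protocol's Table 1 gives an in-hospital data source only, and its outcome list names "Neonatal Status at Discharge (alive or dead)". SAP Table 1 (section 3.1) repeats the in-hospital source: "In hospital: mortality at time of discharge".

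**SAP 8.5.** For Aim 4, "the outcome will be neonatal mortality within 30 days of procedure". The section acknowledges that the protocol used the mother's discharge as the cut-off. Its reason for moving is that "we observed a significant proportion of neonatal deaths after the mother was discharged from the hospital", which it attributes to sick neonates staying longer than well mothers. It continues: "We agreed to include neonatal mortality collected up through 30 day phone follow-up".

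**Timing.** SAP 3.2 describes fieldwork in the past tense: "Data collection for the trial occurred from August 2021 to January 2023".

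**Labels.** SAP section 5 states: "Table 5 lists the original aims along with two aims we added after the publication of the protocol". Those two are the composite and the analysis relating compliance to infection, and only they sit in Table 5's block for analyses not specified in advance. Neonatal mortality stays in the secondary block of Table 5 and again in Table 7.

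**Testing.** Each model is judged at 0.05 without multiplicity adjustment. Section 8.5 carries over the features and interpretation of the primary model.

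**The concern.** An endpoint redefined after trial data have been seen does not have the standing of one fixed in advance. A reader who consults only Tables 5 and 7 would take the Aim 4 result for the protocol's secondary endpoint. The definition that was fixed in advance is neither modelled in this SAP nor deferred to a later paper.

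There is also a practical loss. Death in theatre or on the ward is captured on the intraoperative and inpatient forms and needs no phone call. The 30-day version takes on the audit's incomplete and uneven follow-up, and with it a doubt about what period the outcome covers. The 30-day definition also feeds the Aim 5 composite, although that composite is already labelled as not pre-specified.

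**Working it through.** No sample size or power figure is at issue. The checks are counts, dates and a comparison of definitions.

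**1. Is the protocol endpoint modelled anywhere?** Table 7 lists 1 + 7 + 1 + 1 + 1 + 1 = 12 models, which matches the stated total. One is neonatal, and 8.5 defines it at 30 days. None covers death before discharge. Sections 8 and 9 contain no such analysis, and Table 5 does not list one for future publication.

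**2. Definitions compared**

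| | Protocol outcome 8 | SAP Aim 4 |
|---|---|---|
| Event | newborn or fetal death | neonatal death |
| Window closes | mother's discharge | 30 days after procedure |
| Source | in hospital | through the 30-day phone follow-up |
| Patients | cesarean deliveries | cesarean patients with complete auditor follow-up (section 6) |

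Besides the window, fetal deaths are no longer mentioned and the population is narrower.

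**3. What the audit restriction removes.** Table 4 gives these counts for all enrolled patients, cesarean and other:

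- Control: 2,764 / 5,715 = 48.4% reached; 5,715 − 2,764 = 2,951 dropped (51.6%).
- Intervention: 2,828 / 4,951 = 57.1% reached; 4,951 − 2,828 = 2,123 dropped (42.9%).
- Both: 5,592 / 10,666 = 52.4% reached; 5,074 dropped (47.6%).

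These reproduce the SAP's 48%, 57% and 52%. The gap is widest in cohort 1, at 48% against 71%; in cohort 4 it is 39% against 56%. (Table 3 prints a total of 5,525 where its own conditions sum to 5,592; 5,525 / 10,666 also rounds to 52%.) Cesarean-only counts are not given.

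**4. Can death within 30 days be read from the form?** The outpatient form and its data dictionary ask whether the neonate is alive or dead when the call is made. Neither has a field for date of death. The auditors were trained on the 30-day follow-up tool and called between September 2022 and March 2023 (SAP 4.1). Section 4.2 puts recall at up to a year, and 4.3 and 9.5 say it was longer for controls.

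The dates show how far apart the gaps can be. Take audit launch as 1 September 2022 (Figure 1 note) and assume calls ended on 31 March 2023:

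- Cohort 1 control patients had surgery before 28 December 2021, so their shortest possible gap to a call is 28 December 2021 to 1 September 2022 = 247 days.
- Cohort 5 intervention patients had surgery after 13 September 2022, so their longest possible gap is 13 September 2022 to 31 March 2023 = 199 days.

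If status at the call is what was counted, control neonates had longer in which a death could be recorded. That would tend to favour the intervention. The SAP's argument that long recall is conservative concerns infections being forgotten and does not carry over to this outcome.

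**The case against.** Much of the case for the SAP stands.

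- **Disclosure.** A reader might infer that the switch was hidden. It was not: 8.5 states the protocol definition, the change and the reason together, and SAP Table 1 prints the in-hospital source. Section 5 counts added aims, and reducing neonatal mortality is indeed an original aim. The gap is a missing flag in two tables.
- **Motive.** A reader might infer that the endpoint was chosen for its effect estimate. Nothing in the documents says deaths were viewed by condition. The stated reason is clinical.
- **Planned data item.** Neonatal status after discharge was always to be collected. It is in the protocol's outpatient surveillance and on the 30-day form. Only its use as the endpoint is new.
- **Overlap.** In-hospital deaths among audited women presumably count within the 30-day outcome. What is missing is the separate endpoint, together with deaths among the neonates of women not audited.
- **Weakness of the protocol window.** It closes when the mother leaves, and shortening stay is itself a trial objective. Shorter stays could lower the count with mortality unchanged. A fixed 30-day window avoids this in principle, so the documents do not support making the discharge version the sole Aim 4.
- **Month effects.** The model has 18 month terms. They should absorb the part of the window difference that follows month of surgery, so any remaining difference may be small.

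Two further inferences fail. Ward ascertainment of neonatal death cannot be called complete: no completeness figure is given, and the SAP's remark about robust in-hospital data concerns infections. Nor can the 52.4% coverage be turned into a precision penalty, such as a standard error 1/√0.524 ≈ 1.4 times larger or a need for 1/0.524 ≈ 1.9 times as many deaths. Those factors use all obstetric and gynecologic patients, ignore clustering and month effects, and overlook that 30-day risk is higher than risk before discharge. They also reflect the audit restriction, which Aims 1, 3, 5 and 6 share.

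**Conclusion.** The point holds as one of labelling and of a missing analysis. The endpoint was redefined after neonatal deaths were seen, Tables 5 and 7 do not show it, and 0 of 12 models address the protocol definition. The substituted version leaves out 51.6% of control and 42.9% of intervention patients on the all-patient counts.

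Whether its window is truly 30 days cannot be confirmed from the form. This assumes that the auditors used the form as printed and recorded no date of death elsewhere; if they did record one, the window concern falls away and the labelling point remains. The size of any window bias cannot be stated, because neither death counts nor call times by condition are given.

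The consequence is moderate. This is one secondary outcome, which the SAP itself says may lack power. The documents support neither concealment nor an effect-driven choice.

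**What to change.** 1. Add a model of the protocol endpoint, newborn or fetal death before the mother's discharge, in all enrolled cesarean patients with theatre or ward data. Report it beside the 30-day result, with the number of patients whose in-hospital neonatal status is known in each condition.
2. In Tables 5 and 7, mark the 30-day definition as changed after data were seen and not pre-specified. Update the model count in section 1.2 (Multiple comparisons) from 12 to 13.
3. In 8.5, note that the discharge window depends on length of stay. Say how death within 30 days was established when the form holds only status at the call, and whether fetal deaths are counted.

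The cost is wording, one extra model on data already held, and one more reported estimate. The two results may differ, and the text in 8.5 should prepare the reader for that.
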